## Abstract

*Background*. Lower limb spasticity is a common complication after stroke, which seriously affects the quality of life and rehabilitation of patients. There are different treatment methods for poststroke spasticity. It has been found in clinical practice that governor vessel electroacupuncture (GV-EA) can effectively relieve poststroke upper extremity spasticity, but the efficacy of treatment of lower extremity spasticity needs to be further verified. This study aims to design a randomized controlled trial to evaluate the efficacy of GV-EA in the treatment of poststroke lower limb spasticity. *Methods/Design*. This is a randomized, controlled trial. Patients (*N* = 177) will be randomized to receive routine therapeutic drug and rehabilitation treatment plus GV-EA (experimental group) or routine therapeutic drug and rehabilitation treatment plus EA (control group 1) or routine therapeutic drug and rehabilitation treatment (control group 2). All patients will receive 20 sessions of treatment for 4 weeks. The primary outcomes are the RMS value and the Modified Ashworth Scale. Secondary outcomes include the Fugl–Meyer Assessment for Lower Extremity (FMA-LE) and the Modified Barthel Index score. All outcome measures will be evaluated at the beginning and after the intervention (4 weeks). *Discussion*. This trial will observe the clinical effect of GV-EA on lower extremity spasticity after stroke, especially its influence on surface electromyography characteristics, and provide high-quality experimental evidence for the clinical application of GV-EA based on surface electromyography in the treatment of poststroke lower limb spasticity. *Trial Registration*. China Clinical Trials Registry No. ChiCTR1900027969. Registered on 7 December 2019.

## 1. Introduction

Due to the aging population, accelerated urbanization process, and residents' often-unhealthy lifestyles, there is an increased incidence of stroke [1]. According to statistics, 15 million people worldwide die each year from stroke [2]. Spasticity is one of the most common poststroke complications, and it is also an important cause of motor dysfunction. Among them, lower limb spasticity is manifested as muscle atrophy, pain, and joint contracture stiffness [3, 4]. Although lower limb spasticity is not life-threatening, it has become an important public health issue worldwide because of its high recurrence rate and disability, detrimental effects on functional recovery and quality of life, and high health care costs [5]. Epidemiological surveys have shown that the incidence of lower limb spasticity in Western countries after 6 months of stroke patients was about 42.6%, while as high as 65.7% in China [6, 7]. According to statistics, the medical expenses were 4 times higher for stroke patients with spasticity than those of patients without spasticity [8, 9]. Physical therapy, pharmacological therapies, and botulinum toxin seem to be the most common choices for the treatment of lower limb spasticity. However, every conventional approach has its limitations. There is no uniform standard for the treatment parameters and stimulation intensity of physical therapy. Pharmacological therapies have potential side effects, such as drowsiness, nausea, and vomiting. Long-term injection of botulinum toxin may cause serious adverse reactions such as muscle weakness and dyspnea [10]. Therefore, there is a need for a safer, more effective, and less side effect treatment method for poststroke lower limb spasticity.

Acupuncture has been widely applied to treat poststroke spasticity; it is considered by the World Health Organization (WHO) as an alternative and complementary strategy for the treatment and improvement of stroke [11]. Besides, clinical trials and meta-analysis results have demonstrated that acupuncture can improve balance function, reduce spasticity, increase muscle strength, and improve quality of life [12]. It is also more and more popular with clinicians and patients for its unique advantages of significant efficacy, low price, and small side effects. However, the efficacy differences between different acupoints are uncertain. Few trials have involved the comparison of different acupuncture points to verify the efficacy differences between different acupuncture methods. Governor vessel (GV), also known as “the sea of the yang meridians,” is one of the eight extra meridians. GV passes through the kidney, spinal cord, and brain, so it can treat various system diseases closely related to these parts [13]. Our previous study has demonstrated that GV-EA can significantly reduce the root mean square value of the biceps and triceps and the Modified Ashworth Scale score and increase the Fugl–Meyer Assessment for upper extremity motor function score and the Modified Barthel Index score, which can effectively improve the degree of upper limb spasticity, motor function, and ability of daily life [14]. At the same time, studies in modern medicine have shown that GV-EA effectively increases blood flow and partial pressure of oxygen in the brain, thereby accelerating the self-repair ability of the brain tissue. It also has a protective effect on neuronal damage after cerebral ischemia and promotes brain function reorganization [15].

The methods of clinical assessment of limb spasticity mainly include subjective evaluation methods and objective evaluation methods. Among them, the objective evaluation methods include neurophysiological measures and biomechanical measures. The methods mainly rely on certain instruments to determine the severity of spasticity through corresponding measurement indicators, which can make up for the lack of standardization and precision of subjective evaluation scales [16]. Therefore, we selected acupuncture points frequently used clinically and rehabilitation treatment as the control group to design the clinical trial to explore the efficacy of GV-EA in poststroke lower limb spasticity based on sEMG technology, which can provide a strong evidence-based medical basis for further popularizing the application of GV-EA in the treatment of lower limb spasticity in patients with stroke.

## 2. Methods and Analysis

### 2.1. Trial Design

This is a parallel-design and randomized controlled trial. The subjects will be recruited from the Rehabilitation Center of the First Affiliated Hospital of the Henan University of Chinese Medicine. We selected 177 patients who meet the predefined criteria and randomly divided them into 3 groups, with 59 patients in each group: experimental group (GV-EA), control group 1 (conventional EA), and control group 2 (rehabilitation treatment). All patients will receive 20 sessions of treatment that last for 4 weeks and will have sEMG measurements before and after treatment. The efficacy of GV-EA relative to conventional EA and rehabilitation treatment will be analyzed after data collection. The study flow chart is shown in Figure 1. An example template for the content of admission plans, interventions, and evaluations is shown in Table 1. This protocol is guided by the Standard Protocol Items: Recommendations for Interventional Trials (SPIRIT) [17].

### 2.2. Randomization

All included participants will be randomly assigned to three groups at a ratio of 1:1:1: experimental group and control group 1 and control group 2 following the randomization principle, which employs block randomization to generate random-number sequence using SPSS software and an independent statistician who is not involved in treatment and outcome assessment will be responsible for processing the results. Meanwhile, it prepares predetermined sealed opaque envelopes and these envelopes containing the group information strips will be hidden until informed consent is obtained.

### 2.3. Blinding

This is a single-blinded study; because of the nature of acupuncture treatment, none of the acupuncturists involved in this trial can be blinded to the assignments. Patients will be told that they will receive one of the three effective interventions randomized after enrolment. Each patient will know the type of treatment that they accepted, but they will not know the other two types. The intervention of each patient will be performed in a personal space separated to refrain the communication between patients and will be asked to wear an eye patch when they receive treatment. Data managers and statisticians are not clear on the allocation of patient groups. Therapists, data managers, and statisticians are not allowed to communicate with others about the treatment of patients.

### 2.4. Recruitment

Posters, pictures, and videos related to the study will be produced to help participants understand the purpose and program of this study while explaining the advantages and disadvantages of the treatment and relevant safety measures to be taken during the trial. In addition, we will use websites and hospital-based WeChat ads for recruitment. According to the above-mentioned inclusion and exclusion criteria, we will make a preliminary judgment and screening of the possibility of inclusion for each participant and finally determine whether the subject is included based on the results of the relevant examination.

### 2.5. Inclusion and Exclusion Criteria

#### 2.5.1. Inclusion Criteria

Participants meeting the following criteria will be included:Patients who meet the diagnostic criteria of stroke by computed tomography (CT) or magnetic resonance imaging (MRI) (including ischemic and hemorrhagic stroke).Patients with the Modified Ashworth Scale of grade I and above, grade III and below.First onset, subacute stage of stroke (the onset time is 3 weeks to 6 months).Males or females with an age range between 20 and 70 years.Patients with stable vital signs, no cognitive impairment, and cooperate with treatment.Patients who voluntarily agree and sign the informed consent form.

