### 2.7. Sample Size

The purpose of this study is to evaluate the efficacy of GV-EA in the treatment of poststroke lower limb spasticity. Based on previous studies and clinical experience, the effectiveness rate of conventional EA and rehabilitation treatment is about 75% and 60%, and it is expected that electroacupuncture of GV acupoint will reach 90% [19]. Type 1 error is assumed at 0.05, type 2 error is assumed at 0.1, and a standard deviation is 10. PASS15.0 software (NCSS Statistical Software, Kaysville, UT, USA) has been used to determine the sample size, and the minimum sample size is 53 subjects for each group. Considering a dropout rate of 10%, a total of 177 subjects will be required with 1:1:1 allocation to each group (59 participants per group) for this study.

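### The between-group analysis leaves out time since stroke onset, which varies from 3 weeks to 6 months at entry; this costs precision, not validity

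*Protocol article*

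**What the plan says.** All from the Protocol article.

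- Entry window (section 2.5.1): "First onset, subacute stage of stroke (the onset time is 3 weeks to 6 months".
- Allocation (section 2.2): "All included participants will be randomly assigned to three groups at a ratio of 1:1:1", by a procedure "which employs block randomization to generate random-number sequence using SPSS software". The article names no stratification factor, and it does not say that there is none.
- Setting (section 2.1): one centre, 59 patients in each of three groups.
- Timing (abstract and Table 1): efficacy is assessed twice, before treatment and at 4 weeks.
- Analysis (section 4.4): ANOVA for the comparison among the three groups and Kruskal–Wallis for MAS. No covariate is named. Baseline characteristics are compared by chi-square or ANOVA, but time since onset is not mentioned and no response to an imbalance is described.

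**The concern.** Patients can enter at quite different distances from their stroke. Four weeks of treatment is 4/3 = 133% of the time already elapsed for someone entering at 3 weeks, and 4/26 = 15% for someone entering at about 26 weeks. If spontaneous change over 4 weeks depends on that distance, part of the spread in every outcome is explained by a variable the trial must already collect to establish eligibility. An analysis that ignores it leaves that spread in the error term and so has less power than the same data could give. At stake is the chance of detecting a real difference between arms at the planned size.

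**Working it through.** **1. The plan's own figure.** Section 2.7 assumes 90% for GV-EA and, for the controls, "the effectiveness rate of conventional EA and rehabilitation treatment is about 75% and 60"%, with "Type 1 error is assumed at 0.05, type 2 error is assumed at 0.1, and a standard deviation is 10". For a three-group chi-square test (2 df):

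- mean rate = (0.90 + 0.75 + 0.60)/3 = 0.75
- noncentrality per patient per arm = (0.15² + 0 + 0.15²)/(0.75 × 0.25) = 0.045/0.1875 = 0.24
- noncentrality needed for 90% power at 0.05 = 12.65
- n = 12.65/0.24 = 52.7, so 53 per arm; 53/0.9 = 58.9, so 59; 3 × 59 = 177.

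The stated figures reproduce, and nothing below changes them. The SD of 10 is not used in this calculation.

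**2. Assumptions the documents do not supply.** Onset time is taken as uniform over 3 to 26 weeks, so its SD is (26 − 3)/√12 = 6.64 weeks. The correlation between onset time and 4-week change is set at 0, 0.3, 0.5 or 0.7. The outcome is continuous with SD 1 and all 59 per arm are analysed.

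**3. How far onset time can drift apart by chance.** The standard error of a difference in mean onset time between two arms is 6.64 × √(2/59) = 1.22 weeks, so 95% of randomisations stay within 1.96 × 1.22 = 2.4 weeks. At that limit the arm difference shifts by correlation × 1.96 × √(2/59):

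| Correlation | Shift in SD units |
|---|---|
| 0.3 | 0.11 |
| 0.5 | 0.18 |
| 0.7 | 0.25 |

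For comparison, the standard error of an arm difference is √(2/59) = 0.18 SD.

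**4. False-positive rate** (simulation, 8,000 null trials per cell, nominal 5%):

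| Correlation | Not stratified, plain ANOVA | Balanced on onset time, plain ANOVA |
|---|---|---|
| 0 | 4.7% | 5.0% |
| 0.3 | 4.9% | 3.9% |
| 0.5 | 4.8% | 1.8% |
| 0.7 | 5.2% | 0.2% |

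With adjustment for onset time the rate is about 5% under either allocation. Balancing while keeping the plain ANOVA makes the test conservative, because the error term still contains variation that the design has removed from the arm comparison.

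**5. Power for a 0.5 SD effect in one arm** (simulation, 3,000 trials per cell):

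| Correlation | Not stratified, unadjusted | Not stratified, adjusted | Balanced, adjusted |
|---|---|---|---|
| 0 | 82% | 82% | 80% |
| 0.3 | 80% | 84% | 83% |
| 0.5 | 81% | 90% | 90% |
| 0.7 | 80% | 98% | 99% |

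Differences of a point or two between cells are simulation noise.

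**6. Check by formula.** The noncentrality of the three-arm F test is 59 × 0.5² × 2/3 = 9.83, which gives 80% power. Adjustment divides it by 1 − correlation²: 9.83/0.91 = 10.81, 9.83/0.75 = 13.11 and 9.83/0.51 = 19.28, which give 84%, 91% and 98%. In sample-size terms, 59 per arm with adjustment is worth about 59/0.91 = 65, 59/0.75 = 79 or 59/0.51 = 116 per arm without it.

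**The case against.** A reader might infer more: that without stratification an excess of early patients in one arm will be mistaken for a treatment effect. The documents do not support that. Allocation is random, so imbalance in onset time is chance error, and step 4 shows that the test at 0.05 already allows for it. Control group 2 receives the same routine care and is assessed at the same two times, so natural recovery is present in all arms. It is true that if half of patients count as early (an assumption), two given arms of 59 differ by at least 10 percentage points in early patients about 31% of the time, and some pair of the three does about 57% of the time. Those are chances of a covariate gap, not of a wrong conclusion.

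A narrower version has some force. The 5% is an average over randomisations. If the realised imbalance between two arms sat at its 95% limit, the unadjusted pairwise false-positive chance would be about 8%, 13% or 21% at correlations 0.3, 0.5 or 0.7. That is another reason to adjust, but not evidence that the procedure is invalid.

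Three further objections stand in part:

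- Nothing in the documents shows that 4-week change in MAS, RMS, FMA-LE or MBI differs between early and late entrants. The 6-month incidence in the Introduction ("the incidence of lower limb spasticity in Western countries after 6 months of stroke patients was about 42.6"%) does not bear on it. The correlation therefore remains an assumption.
- A journal article commonly condenses allocation details, so silence on strata is no fault. The point rests instead on section 4.4, which names the between-group tests; the full analysis plan may add a covariate that the article omits.
- Stroke type, MAS grade and age also vary under section 2.5.1. The choice of onset time rests on clinical plausibility, not on data in the article.

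**Conclusion.** A minor point about efficiency. As described, the analysis stays valid at 5% and the sample size is unaffected, but a baseline variable available for every patient is left out of the between-group comparison. The cost depends wholly on a correlation the documents do not give. At 0.3 adjustment lifts power for a 0.5 SD effect in one arm from about 80% to about 84%, at 0.5 to about 90%, at 0.7 to about 98%; at 0 there is essentially nothing to gain or lose. These figures assume uniform entry over 3 to 26 weeks, a linear relation, a continuous outcome and 59 analysed per arm. They carry over only loosely to MAS, which is ordinal. Adjustment alone recovers nearly all of the gain; stratified allocation adds almost nothing to it.

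**What to change.** In section 4.4, pre-specify time since onset as a covariate in the between-group model (ANCOVA) for RMS, FMA-LE and MBI. For MAS, Kruskal–Wallis has no place for a covariate, so replace it with a method that does, such as an ordinal logistic model or a rank-based ANCOVA.

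Stratifying the block sequence in section 2.2 by onset time is an optional complement. If it is done, use it only together with the adjusted analysis, for the reason shown in step 4.

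The cost is one model degree of freedom for each outcome and a changed test for MAS, which is a primary outcome, so the change should be fixed before any comparative data are seen. No new data collection is needed and 53/59/177 stays as it is. Stratification, if chosen, adds a second envelope series at the single centre.

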#### 2.5.2. Exclusion Criteria

Participants will be excluded if they meet any of the following criteria:Patients with other serious diseases that may affect treatment outcomes and life-threatening, such as cardiac disease, hepatic disease, pulmonary disease, renal disease, diabetes, osteoporosis, or bleeding tendency.Patients with systemic infection, or severely unstable.Patients who are pregnant, lactating, or preparing for pregnancy.Patients with severe cognition obstacles who cannot cooperate with the treatment.Patients who are participating in other clinical trials.

### 2.6. Interventions

The trial is divided into 3 groups, namely, experimental group (GV-EA group), control group 1 (conventional EA group), and control group 2 (rehabilitation treatment group). These three groups of patients will receive different treatments 5 times a week for 4 weeks in separate compartments. Meanwhile, each patient will receive the same routine therapeutic drug and rehabilitation treatment. In addition to these two treatments, the experimental group also has electroacupuncture on governor vessel acupoints, and the control group 1 has electroacupuncture on conventional acupoints.

#### 2.6.1. Routine Therapeutic Drug Treatment

All patients use blood pressure control, blood lipid adjustment, blood sugar control, and nutritional nerve drug as routine therapeutic drug treatment following the physicians' instruction.

#### 2.6.2. Rehabilitation Treatment

According to the actual situation of all patients, we will follow the theory of neurodevelopment and provide each patient with the same rehabilitation treatment that will include the affected limb position, passive stretching exercises, muscle strength training, proprioceptive neuromuscular facilitation exercises, Bobath therapy exercises, and Brunnstrom therapy exercises.

#### 2.6.3. Acupuncture Interventions

In China, stroke patients are familiar with acupuncture treatment. Thus, it is easy for patients to determine whether fake acupuncture is used. And because an important purpose of this trial is to make up for the lack of comparison of the efficacy differences between different acupuncture acupoints in the current experiment, placebo acupuncture was not selected. Therefore, we decided to perform clinical conventional electroacupuncture as the control group rather than sham acupuncture and placebo acupuncture.

The interventions will be performed by acupuncturists with more than 3 years of experience in rich clinical acupuncture practice. The acupuncture treatment group used sterilized stainless steel disposable acupuncture needles (0.3∗30 mm). After the needle is inserted to a certain depth of points, it will be lifted and thrust or twirled and rotated for Deqi sensation. After feeling of “Deqi”(the sensations including soreness, numbness, distention, or heaviness), it was connected to the electroacupuncture device (G6805-2A, Shanghai Huayi Medical Instrument Co., Ltd., China, dense waves 2–5 times/second, frequency 2.5 Hz), once a day, every 30 minutes, 5 times a week, for 4 weeks.

#### 2.6.4. Experimental Group

In addition to the two routine treatments, acupuncture will also be performed at Dazhui (GV14), Shendao (GV11), Jinsuo (GV8), Mingmen (GV4), and Yaoyangguan (GV3) for patients in the experimental group. The specific operation method is as follows: generally take the prone position, punctured obliquely to a depth of 0.5–1.0 cm. After the needle is inserted, manipulations will be applied for the “Deqi” sensation. The locations are specifically presented in Table 2.

#### 2.6.5. Control Group 1

The acupuncture will also be performed at the hemiplegic side Blood sea (SP10), Zusanli (ST36), Yinlingquan (SP9), Yanglingquan (GB34), and Sanyinjiao (SP6) for patients in control group 1. The selected acupoints in this group were high-frequency acupoints based on data mining, the clinical experience of famous acupuncturists of the past, and theoretical research of Chinese medicine for acupuncture treatment of poststroke spasticity [18]. Specific operation: generally take the supine position, perpendicular insertion 1.0–1.5 cm. After “Deqi”, the electrode will be connected to the needle.

#### 2.6.6. Control Group 2

Control group 2 only received the two routine treatments.

### 2.7. Sample Size

The purpose of this study is to evaluate the efficacy of GV-EA in the treatment of poststroke lower limb spasticity. Based on previous studies and clinical experience, the effectiveness rate of conventional EA and rehabilitation treatment is about 75% and 60%, and it is expected that electroacupuncture of GV acupoint will reach 90% [19]. Type 1 error is assumed at 0.05, type 2 error is assumed at 0.1, and a standard deviation is 10. PASS15.0 software (NCSS Statistical Software, Kaysville, UT, USA) has been used to determine the sample size, and the minimum sample size is 53 subjects for each group. Considering a dropout rate of 10%, a total of 177 subjects will be required with 1:1:1 allocation to each group (59 participants per group) for this study.

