### 2.9. Primary Outcomes

The main result is surface electromyography (sEMG) measurement and the Modified Ashworth Scale (MAS).

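### The 90% power in section 2.7 belongs to a comparison of effectiveness rates that the trial does not analyse, and the SD of 10 plays no part in it; power for RMS and MAS is undocumented

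*Protocol article*

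**What the plan says.** Section 2.7 (Sample Size) states that "the effectiveness rate of conventional EA and rehabilitation treatment is about 75% and 60" per cent respectively, and that "it is expected that electroacupuncture of GV acupoint will reach 90" per cent. It continues: "Type 1 error is assumed at 0.05, type 2 error is assumed at 0.1, and a standard deviation is 10". From these inputs it reports that "the minimum sample size is 53 subjects for each group", and raises this to 59 per group and 177 in total for 10% dropout.

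Section 2.9 names the primary outcomes: "The main result is surface electromyography (sEMG) measurement and the Modified Ashworth Scale (MAS"). Section 3.1 names FMA-LE and MBI as secondary. Table 1 schedules RMS, MAS, FMA and MBI as the efficacy assessments.

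Section 4.4 assigns paired t-tests and a three-group ANOVA to RMS, FMA-LE and MBI, and Kruskal–Wallis to the MAS. It mentions a chi-square test only for baseline data.

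**The concern.** A power statement means something only for a named outcome and a named test. Section 2.7 works with a binary response, whereas every efficacy outcome in the article is a measurement or a score and no efficacy comparison of proportions is planned. The same sentence also gives an SD, which belongs to a comparison of means, but no mean difference, unit or outcome goes with it.

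The interpretation of the result is at stake. If RMS or MAS shows no difference, a reader will take the 90% in section 2.7 as assurance that a relevant effect would probably have been found. The article gives no basis for that assurance, because it states no expected difference or SD for RMS and no expected distribution for the MAS.

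**Working it through.** **Inputs (all from section 2.7).** Rates 0.90, 0.75 and 0.60; alpha 0.05; type 2 error 0.1; SD 10; 53 per group before dropout; dropout 10%; allocation 1:1:1.

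**1. Reproducing the plan's figure from the rates alone.**
- Mean rate = (0.90 + 0.75 + 0.60)/3 = 0.75.
- w² = [(0.15² + 0² + 0.15²)/3] / (0.75 × 0.25) = 0.015/0.1875 = 0.08, so w = 0.283.
- The omnibus chi-square test has 2 df and noncentrality N × w².
- 52 per group: noncentrality 156 × 0.08 = 12.48, power 89.6%.
- 53 per group: noncentrality 159 × 0.08 = 12.72, power 90.2%.

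So 53 is exactly the smallest group size that reaches 90%, and no SD was used. For dropout, 53/0.90 = 58.9, rounded up to 59, and 3 × 59 = 177. Both stated totals follow.

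**2. Could another route give 53?** Pairwise tests of proportions (two-sided 0.05, 90% power) need 133 per group for 90 v 75%, 42 for 90 v 60% (49 with continuity correction) and 203 for 75 v 60%. The only other near matches are 90 v 60% at a Bonferroni alpha of 0.0167, which the article does not state: 54 or 52 two-sided, depending on the formula, and 53 one-sided with continuity correction. None of these uses an SD either.

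**3. Could the SD of 10 have produced 53?** Read 90, 75 and 60 as means with SD 10. Then f = √[(15² + 0² + 15²)/3]/10 = √150/10 = 1.22, and ANOVA needs about 5 per group for 90% power. A pairwise comparison of a 15-point difference needs 10 per group. To arrive at 53, the SD would have to be about 42 to 43.5 (ANOVA) or 23.75 (pairwise). An SD of 10 does not lead to the stated figure.

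**4. What was sized against what will be tested.**

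| | Section 2.7 | Sections 2.9, 3.1, 4.4 and Table 1 |
|---|---|---|
| Outcome | effectiveness rate, undefined | RMS and MAS primary; FMA-LE and MBI secondary |
| Test | consistent with a three-group chi-square | ANOVA for RMS; Kruskal–Wallis for MAS |
| SD | 10, no outcome or difference | none stated |

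**5. What 53 evaluable per arm delivers for the planned RMS test.** For a three-group ANOVA at 0.05 (N = 159; 2 and 156 df), solving the noncentral F for 90% power gives f of about 0.285. In terms of the gap d between the extreme arms, in SD units:
- Means equally spaced: f = d/√6, so d = 0.285 × 2.449 = 0.70 SD.
- One arm different from two equal arms: f = d × √(2/9), so d = 0.285/0.471 = 0.60 SD.

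As a yardstick only, a two-sample t-test with 53 per arm has 90% power for 0.64 SD at two-sided 0.05, or 0.69 SD at 0.025. Section 4.4 names no pairwise test between groups.

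No corresponding figure can be given for the MAS. It is a six-level ordinal score tested by ranks with many ties, and the article gives no expected distribution.

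**The case against.** The best defence is that the arithmetic is sound: 53, 59 and 177 all follow from the stated rates. That stands, and this point alleges no calculation error.

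It can also be said that an effectiveness rate could be derived from the change in MAS, and that an article condenses its full protocol. A derivation is possible. But section 4.4 does state how the MAS will be compared between groups, and it is not by a responder rate. The conflict is between statements the article makes, so it does not depend on detail left out.

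Three stronger readings are tempting and are not supported:
- **That the trial is too small.** Nothing in the article shows that 59 per arm is inadequate for RMS or MAS. The article gives no expected effect on either outcome, so the power is undocumented and cannot be called low.
- **That the SD of 10 is impossible because the MAS is coded 0 to 5.** Section 2.7 does not attach the SD to the MAS or to any other outcome. The supportable criticism is that it is attached to nothing.
- **That the trial can simply be said to have 90% power for 0.64 SD on RMS or MAS.** That figure belongs to a two-sample t-test. It is not what the three-group ANOVA delivers under either pattern above, and it does not carry over to a rank test on the MAS.

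That the SD was unused, and that the three-group chi-square was the method, are inferences from a numerical match. The match is exact, but the authors should confirm the method.

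**Conclusion.** The point holds as a mismatch of outcome and test, together with a stray input. The 90% power applies to an omnibus comparison of 90%, 75% and 60% (90.2% at 53 per group), and that comparison is not among the planned analyses. It does not describe the ANOVA on RMS or the Kruskal–Wallis test on the MAS.

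For RMS, the size supports a statement only in standardised units: f of about 0.285 at 90% power. This assumes 53 evaluable patients per arm, normal errors with a common SD, and alpha 0.05 spent on that one test. Whether such an effect is plausible or relevant cannot be judged from the article.

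**What to change.** Keep 59 per arm and revise section 2.7 as follows.

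1. Delete the SD of 10, or tie it to a named outcome and a stated difference.
2. Keep the effectiveness rates and say that 53 per group came from a three-group chi-square test on them, once the authors confirm this. Deleting the rates would hide how the size was chosen.
3. Then take one of two routes:
   - define the effectiveness rate from the MAS and add its three-group comparison to section 4.4 as an analysed outcome; or
   - state that the 90% power does not apply to RMS or MAS, and report what the size gives for the planned RMS test. Possible wording: *With 53 evaluable patients per arm, the three-group ANOVA of RMS at 0.05 has 90% power for f of about 0.285, that is, extreme arms about 0.70 SD apart if the means are equally spaced, or 0.60 SD apart if one arm differs from two equal arms.*
4. Label any pairwise figure (0.64 SD at 0.05, 0.69 SD at 0.025) as a two-sample t-test yardstick, and claim no SD-based power for the MAS.

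The second route needs only rewording. The first also adds a defined outcome and one analysis, using MAS data already scheduled. Neither needs more patients or visits. The price is that the section can no longer claim 90% power for the primary outcomes without qualification.
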